### Some relevant properties of Standard Indonesian

Indonesian is a zero-marking language [20] without case or gender markings. Transitive verbs are usually only inflected for voice (active or passive), and there is no verb inflection for tense, aspect, or agreement. Indonesian has SVO word order [21]; however, the ordering of constituents can be flexible, and it is possible (although infrequent) for verbs to take the initial position. Chung [22] suggested that Indonesian belongs to a branch of the Austronesian language family that was originally verb-initial, as the passivized transitive, active-transitive, as well as intransitive verbs can take the 1^st^ position.

The usual transitive passive (5b) has the patient in the initial position. Examples of typical simple active and simple passive sentences are as follows:

5a) Simple active (agent-patient / SVO)
Perempuan    itu    **men**dorong    laki-laki    itugirl    the    **ACT**-push    boy    the‘the girl is pushing the boy’5b) Simple passive (patient-agent / OVS)
Laki-laki    itu    **di**dorong    (oleh) perempuan    ituboy    the    **PAS**-push    (by)    girl    the‘the boy is pushed by the girl’

The canonical sentence (5a) contains a verb with an active-transitive voice marking (*men-*). Likewise, the passive is expressed by the prefix (*di-*) on the verb in (5b), where ‘the boy’ is the patient of the action. Similar to English, the by-phrase is optional in the passive. In addition, the preposition (*oleh*) ‘by’ may be omitted when the agent is immediately adjacent to the verb (Cole & Hermon, 2008). As the current study observes the ERP distinctions between the simple active and the simple passive, it is also worth noting that the typical passive in Indonesian, unlike in most Indo-European languages, is highly frequent. It is acquired at a very early stage (around 2 years old; [23]) compared to English (4–5 years old), which can be attributed to its high input frequency of 28–35% in Indonesian, compared to 4–5% in English. This difference is also reflected in the written form: Only 9% of English verbs display passive morphology [24] compared to 30–40% of Indonesian verbs [25] having the passive marker ‘*di-*‘.

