### Materials

Participants will read stimuli comprising 100 semantically reversible active and passive sentences (see S1 Appendix in S1 File). Examples of which are shown in Table 2.

**Table 2 pone.0272207.t002:** Stimuli examples of each condition.

Condition	NP1	Art	VP	Adjunct	NP2	PP/RC
Active	Polisi	itu	menembak	langsung	seorang perampok	di malam hari.
	Police	that/the	**ACT**shoot	immediately	(a) robber	at night.
		(the/a) police immediately shoots (the/a) robber at night.				
Passive	Polisi	itu	ditembak	langsung	oleh perampok	di malam hari.
	Police	that/the	**PAS**shoot	immediately	by robber	at night
		(the/a) police is immediately shot by (the/a) robber at night				

The sentences involve an animate subject and object and are constructed while avoiding a plausibility bias. Word order is manipulated by using two structures: simple active and simple passive sentences. Based on previous studies on processing well-formed sentences, the contrast of interest is passive-active, and whether the effects of the word order persist. We will strive for active-passive pairing plausibility with the use of NP1 and NP2 that are plausibly reversible (i.e. each sentence should not be strongly biased to one interpretation due to the nouns used). Additionally, there will be 200 filler trials consisting of questions (e.g. What did the adventurer notice yesterday?) and cleft sentences (e.g. it is the boy who the girl is calling) to prevent the habituation of the participants. The task for both the experimental and filler sentences will be discussed in the Procedure. The stimuli will be tested for acceptability and prototypicality using an online survey method utilizing a Likert scale of 1 to 7 with a similar setup used by Jackson, Lorimor, & van Hell [15]. Assuming the materials are rated acceptable and plausible by raters, the materials will not be further edited.

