The materials will be presented visually and word-by-word for 500ms with a 100ms blank screen between each word. Each trial begins with a blank screen of 750ms followed by the word ‘*siap*?’ (ready?), which stays on the screen until participants presses any keys. There will be two lists of sentences each pseudorandomized into 10 sets (each set containing 10 experimental sentences and 20 fillers). Digital triggers will be manually inserted at three time points in every sentence: at the onset of the verb (i.e., the onset of the prefix), and at the onset of NP2. Additionally, NP1 data points will be extracted from -1400 to -200 before the verb onset to be used as a sanity check to see if there are baseline differences between the conditions. It is important to note that the triggers will be located in the middle of the sentence.

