The EEG data will be re-referenced to the two mastoid electrodes. The ERPs will be calculated per participant, per electrode, and per condition in intervals of 200ms before onset to 1000ms after onset for each time-locked trigger. These epochs will then be demeaned per channel in each epoch (the mean of the data from the entire epoch will be subtracted from each data point, as this may result in better ICA decompositions than baseline-correcting based on pre-stimulus interval; [40]. The epochs will then be subjected to an independent component analysis using the runica() command in EEGLAB [41]; this will divide the data into many independent components corresponding to the number of channels, excluding mastoid electrodes, EOGs, and bad channels that are previously marked. These components will be inspected visually to identify blinks and saccades, and components that are identified as blinks or saccades will be removed (a maximum of four components per participant can be removed, and if the number of components removed exceeds this, the participant will be excluded from the analysis). After the removal of components corresponding to blinks and saccades, baseline correction will be applied to the data with a 200 ms pre-stimulus onset baseline. Next, the epochs will be run through a moving window peak-to-peak threshold function for artefact detection; epochs with artifacts will be marked for removal based on this criterion. Lastly, the data will be filtered using a 0.1–40.0 Hz bandpass filter via the pop_eegfiltnew() default EEGLAB function.

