In general, for the time windows and specific components, due to the nature of cluster-based permutation where adjacent sites and time points are correlated, we will be looking at the whole epoch (here we theorize that a ‘real’ effect should persist through multiple adjacent electrodes and a chunk of tens to hundreds of milliseconds/samples–a more detailed description of the procedure is provided by [45]). However, were there to be an effect in either the verb or NP2 (as per the predictions above), we expect it to be observed in the time windows and distributions corresponding to the LAN, N400, and/or P600 –all of which have been observed in similar studies and above 300ms. Specifically, for the verb, we would expect the passive to be more positive than the active for the 500-700ms time window, as this was what the study closest [15] to this one reported in their critical region. For NP2, we expect some form of negativity to occur for the passive compared to the active between the 300-600ms time window–this was observed in studies which reported ERPs post-disambiguation.

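### On the Table 2 template the NP2 trigger falls on different words in actives and passives, and the predicted 300-600 ms window closes as the shared noun appears, so an NP2-onset effect cannot be separated from the function-word difference

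*Protocol article*

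**What the plan says.** Materials fixes the presentation rate: "The materials will be presented visually and word-by-word for 500ms with a 100ms blank screen between each word". Triggers are set "at the onset of the verb (i.e., the onset of the prefix), and at the onset of NP2". The Table 2 example fills the NP2 column with "seorang perampok" (active) and "oleh perampok" (passive), with an adjunct between the verb and NP2 in both.

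The section on properties of Standard Indonesian says that the passive preposition "may be omitted when the agent is immediately adjacent to the verb". EEG recording and preprocessing computes ERPs "in intervals of 200ms before onset to 1000ms after onset for each time-locked trigger", with a 200 ms baseline before each trigger. The statistical analysis plan section tests the whole interval after the trigger at all scalp electrodes.

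Predictions states: "For NP2, we expect some form of negativity to occur for the passive compared to the active between the 300-600ms time window". The second prediction there attributes an NP2 contrast to greater processing cost of the non-canonical structure. The third concludes that earlier findings were confounded by frequency if neither the verb nor NP2 shows a difference. The present study section gives NP2 a supporting role, as a place to look for spill-over from the verb.

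**The concern.** A contrast at a trigger isolates voice only if what is on the screen is otherwise comparable. On the Table 2 template, the NP2 trigger sets the response to a determiner against the response to a preposition. These differ in identity, word class and length, and the frequency control described in the article covers verbs only. The one word that the two NP2 columns share, the noun, comes on a full word-slot later.

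Two conclusions are exposed. A purely lexical *oleh*/*seorang* difference could be reported as support for the second prediction. The same difference could also stop the authors from drawing the third, because that one requires nothing at NP2 as well as nothing at the verb. The permutation test gives no protection: it controls false positives when the conditions do not differ, and different words can produce a real difference.

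**Working it through.** **Inputs.** Word 500 ms plus blank 100 ms (Materials). Word order and NP2 content (Table 2). Epoch -200 to 1000 ms (EEG recording and preprocessing). Predicted NP2 window 300-600 ms (Predictions).

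**Step 1: reproduce the article's own timing figure.** The onset-to-onset interval is 500 + 100 = 600 ms. In Table 2 the NP1 noun is two words before the verb, so its onset is -2 × 600 = -1200 ms. The epoch around it runs from -1200 - 200 = -1400 to -1200 + 1000 = -200 ms. This matches the stated NP1 extraction window (-1400 to -200) exactly. If noun and article shared one screen, the window would be -800 to +400 ms, which does not match. Function words therefore have their own 600 ms slot.

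**Step 2: place each word.**

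| Active | Passive | ms from verb onset | ms from NP2 trigger |
|---|---|---|---|
| menembak | ditembak | 0 | -1200 |
| langsung | langsung | 600 | -600 |
| seorang | oleh | 1200 | 0 |
| perampok | perampok | 1800 | 600 |
| di | di | 2400 | 1200 |

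**Step 3: the predicted window.** Relative to the noun, 300-600 ms after the NP2 trigger is 300 - 600 = -300 to 600 - 600 = 0 ms. The window closes at noun onset and contains no noun-evoked activity.

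**Step 4: the rest of the NP2 epoch.** It ends 1000 - 600 = 400 ms after noun onset. A 300-600 ms window locked to the noun lies 900-1200 ms after the NP2 trigger, so 1000 - 900 = 100 of its 300 ms is inside the epoch.

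**Step 5: the verb epoch.** It ends 1000 ms after verb onset, and the differing function words start at 1200 ms. The only other word inside it is *langsung*, which is the same in both conditions. The mismatch does not reach the verb contrast.

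**Step 6: consequences for a remedy.** A 200 ms baseline immediately before the noun covers 600 - 200 = 400 to 600 ms after the differing function words, so the mismatch would move into the baseline. Adding a determiner to the passives alone would put their noun at 1800 + 600 = 2400 ms after the verb, against 1800 ms in the actives.

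**The case against.** Several objections have weight.

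- **NP2 is secondary.** The verb is the main region, the Abstract ties its conclusion to the verb prefix, and the first prediction stands without NP2. This stands and limits the severity. It does not remove the problem, because the second prediction and the null branch both use NP2.
- ***Oleh* belongs to the passive.** With an adjunct after the verb, the article's condition for omitting it is not met, so some difference here comes with the voice contrast as built. That is fair, but NP2 is there to detect spill-over, and spill-over cannot be told apart from the response to a different word.
- **The test covers 0-1000 ms; 300-600 ms is only where an effect is expected.** This stands. A cluster at 600-1000 ms could include a noun response, though only its first 400 ms.
- **Table 2 is an example.** The item list in S1 Appendix is not shown, and active example 5a has a second noun phrase without *seorang*. The determiner and definiteness contrast is therefore not established across items. Any passive with an intervening adjunct would still be expected to begin NP2 with *oleh*, and the active would not.
- **Trigger placement is not fully pinned down.** The text announces three time points but names two, and it does not say whether NP2 onset in passives means the preposition or the noun. The Table 2 column makes the preposition the likelier reading.

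A reader might infer that any NP2 effect would simply be the function-word response, or that the study's main result is compromised. The documents support neither. Carry-over from the verb, 1200 ms earlier, could also contribute, and the verb contrast is untouched.

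**Conclusion.** The point holds as a limit on attribution in a secondary region. On the Table 2 template the NP2 trigger marks different words in the two conditions, and the predicted window has 0 of its 300 ms after noun onset. A passive-active difference there cannot be separated from the function-word difference. It should not, by itself, be read as a processing cost of non-canonical structure or used to reject the frequency account.

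This rests on three assumptions: one word per 600 ms slot, which the NP1 window confirms; the NP2 trigger at the first word of the NP2 column; and an item set that follows the Table 2 template, which needs checking. It does not establish that an NP2 effect would be purely lexical.

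**What to change.** 1. Check the full item list to see which word opens NP2 in each active and passive item, and state in Materials which word carries the NP2 trigger.
2. Add a trigger at the NP2 noun. On the Table 2 template it is the same word at the same position, 1800 ms after verb onset, in both conditions. Apply the predicted 300-600 ms window to this epoch.
3. Baseline that epoch on the common pre-verb interval rather than on the 200 ms before the noun.
4. Do not add a determiner to the passives only, since that would shift their noun by 600 ms.
5. Report the NP2-onset contrast as descriptive. State in Predictions that it cannot alone support the second prediction or rule out the third.

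The cost is one extra trigger per sentence and a few sentences of text; no item needs rewriting. The downside is more exposure to slow drift, because the baseline ends 1800 ms before noun onset. Late activity from the function words may also still be present, since the noun-locked window lies 900-1200 ms after them. The noun epoch therefore makes attribution cleaner but does not settle it completely. The item check is best done before the rating survey, because Materials says that items rated acceptable and plausible will not be changed afterwards.

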### Statistical analysis plan

The statistical analysis will be conducted using cluster-based permutation tests [45] over all the scalp electrodes and the entire post-stimulus epoch. The advantage of this approach is that it allows testing for effects anywhere on the scalp and any time in the epoch, while still controlling the familywise false positive rate, and without the experimenter needing to choose regions and time windows for analysis. The test works by comparing the active and passive ERPs at each channel and each sample and identifying clusters of spatiotemporally adjacent data points where the difference between the two conditions exceeds some threshold; in our analysis, that threshold will be two-tailed p < .1 in a t-test. In other words, a t-test comparing active and passive will be performed at every sample in every channel, if a series of several time points in a row on the same channel and/or several adjacent channels at the same time all exceed this threshold, they are treated as a "cluster". Next, each cluster is assigned a test statistic (in our case, the test statistic for a cluster is derived by summing the *t*-values of all the samples in the cluster), and the largest cluster-level test statistic in the epoch is taken as the observed test statistic for the data. Next, the data are randomly permuted (i.e., within each subject, the condition labels "active" and "passive" may be randomly switched) several thousand times, and with each random permutation the abovementioned procedure of identifying clusters and calculating a test statistic is repeated. This yields a permutation distribution of several thousand test statistics, against which the original observed test statistic is compared. The proportion of permutation test statistics that are larger than the original observed test statistic is the *p*-value for the test; if there is a significant difference between the active and passive ERPs then this value will be small. See [45] for a more detailed explanation of how this test works.

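### The pre-verb sanity check stops at -200 ms, where the verb's own baseline begins, so it cannot rule out an active-passive difference in the interval subtracted from the critical ERP

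*Protocol article*

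**What the plan says.** All of the relevant text is in the Method part of the protocol article.

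- **The check (Materials).** "NP1 data points will be extracted from -1400 to -200 before the verb onset to be used as a sanity check". Its stated aim is "to see if there are baseline differences between the conditions".
- **Word timing (Materials).** Sentences appear "word-by-word for 500ms with a 100ms blank screen between each word".
- **Words before the verb (Materials, Table 2).** The active example opens "Polisi itu menembak". The passive example has the same two words before its verb.
- **Epochs (EEG recording and preprocessing).** ERPs are computed "in intervals of 200ms before onset to 1000ms after onset for each time-locked trigger".
- **Baseline (same section).** After removal of eye-movement components, "baseline correction will be applied to the data with a 200 ms pre-stimulus onset baseline". The section also discusses how differences before the critical word can distort a mid-sentence baseline. It weighs the alternative of stronger filtering without a baseline, and keeps the 200 ms baseline.
- **Test (Statistical analysis plan).** The cluster-based permutation test runs "over all the scalp electrodes and the entire post-stimulus epoch".

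**The concern.** The check is there to find out whether the two voices already differ before the verb. The part of the pre-verb signal with the most direct effect on the verb result is the 200 ms that is subtracted from each verb epoch, and the check ends where that interval starts.

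Nothing else in the article fills the gap. The permutation test uses post-stimulus samples only. Within the verb epoch, baseline correction sets the mean of -200 to 0 ms to zero in each voice, so a mean difference there can no longer be seen.

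The verb contrast carries the main prediction: passive more positive than active at 500-700 ms. A baseline difference enters that contrast with reversed sign as an offset across the epoch. Depending on its sign, it could add to the predicted positivity or cancel part of it. Cancellation matters because the Predictions section reads an absence of effects at both the verb and NP2 as evidence that earlier findings were confounded by frequency. The cluster-forming threshold of p < .1 was chosen to favour small, long-lasting effects, and an offset is long-lasting.

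A chance imbalance is possible even though the pre-verb words match in the example. The Data exclusion criteria accept participants with as few as 25 of 50 trials per condition, so the first nouns left after artefact rejection need not be the same in both voices.

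**Working it through.** **1. Reproduce the stated window.**

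- Time per word = 500 + 100 = 600 ms (Materials).
- Words before the verb = 2 (Table 2 example), so NP1 onset = -2 × 600 = -1200 ms and *itu* onset = -600 ms.
- Standard epoch = -200 to +1000 ms around onset (EEG recording and preprocessing).
- Around NP1: -1200 - 200 = -1400 ms and -1200 + 1000 = -200 ms.

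This gives exactly the stated -1400 to -200 ms. The window is the general epoch placed on NP1. With one word before the verb the same rule would give -800 to +400 ms, and with three words -2000 to -800 ms, so the stated limits fit two-word openings.

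**2. Overlap with the verb baseline.**

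- Check window = [-1400, -200]; verb baseline = [-200, 0].
- Overlap = max(0, min(-200, 0) - max(-1400, -200)) = max(0, -200 + 200) = 0 ms.

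Both intervals are defined relative to verb onset, so this result does not depend on the number of words before the verb.

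**3. What the check does cover (two-word opening).**

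| Part | Interval (ms) | Covered |
|---|---|---|
| Before NP1 | -1400 to -1200 | 200 ms |
| NP1 slot | -1200 to -600 | 600 of 600 ms |
| *itu* slot | -600 to 0 | 400 of 600 ms |
| Pre-verb sentence in total | -1200 to 0 | 1000 of 1200 ms = 83% |

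**4. Effect of a difference in the uncovered interval.** Let D(t) be the passive minus active wave before baseline correction, and d its mean over -200 to 0 ms. After correction, D*(t) = D(t) - d for every t from 0 to 1000 ms. For example, d = -1 µV adds +1 µV throughout, and d = +1 µV removes 1 µV throughout. This holds at the correction step; the 0.1-40 Hz filter is applied later. The mean of D* over -200 to 0 ms is d - d = 0, whatever d was.

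**5. Illustration of what the check can and cannot show.** The assumptions, none of which the article gives apart from n = 50, are:

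- difference-wave SD of 2 µV per participant;
- autocorrelation time of 200 ms;
- true difference of 1 µV;
- paired test on the mean over -600 to -200 ms (a simple stand-in for the cluster test);
- 1000 simulated studies per case.

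| Where the 1 µV difference lies | Flagged, check baselined on -1400 to -1200 ms | Flagged, no baseline |
|---|---|---|
| Sustained from NP1 onset | 0.866 | 0.991 |
| Only -200 to 0 ms | 0.056 | 0.046 |

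A sustained difference is usually found. One confined to the verb baseline is flagged at about the 5% false-positive rate. The first row depends on the assumed SD and correlation time. The second does not, because the difference lies wholly outside the checked window.

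**6. After extension to verb onset.** Overlap with the verb baseline rises from 0 to 200 of 200 ms, and coverage of the pre-verb sentence from 1000/1200 (83%) to 1200/1200 (100%).

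**The case against.** The strongest reply is that a systematic difference limited to the last 200 ms is unlikely. In the example the words before the verb are identical, and voice is first marked by the verb prefix. A lexical or list imbalance would arise at -1200 or -600 ms, inside the checked window, and a slow drift would not normally be confined to -200 to 0 ms. This stands, and it limits the weight of the point. It does not remove it, because the check exists to confirm that expectation and leaves out the interval with the most direct effect.

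Second, random baseline noise enters both the observed statistic and the label-swapped statistics, so it is already in the permutation null. This also stands: noise costs precision and does not raise the familywise error rate.

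Third, an offset might be noticed. It would be present from 0 ms, whereas real effects are expected after 300 ms, and a slope or change of shape within -200 to 0 ms survives the correction. That helps a careful reader but is not a planned check, and it would not reveal an offset that cancels a true effect.

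Fourth, the article discusses distorted baselines openly and justifies its choice. That is a reason for the accompanying check to include the baseline it defends.

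A reader might go further and infer that the check cannot detect what it is meant to detect. The documents do not support this, since it covers 83% of the pre-verb sentence. A reader might also infer that the key press contaminates the start of the window, because the ready prompt is one "which stays on the screen until participants presses any keys". The interval from key press to first word is not stated, and a condensed article may omit it. Such activity would in any case be common to both voices and add noise, not an active-passive bias.

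**Conclusion.** The point holds in a limited form. The check and the verb baseline overlap by 0 ms, so the check cannot rule out an active-passive difference in the interval subtracted from the critical ERP. A mean difference d there moves the verb difference wave by -d at baseline correction. Differences that begin at NP1 or early in *itu* and persist remain detectable.

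The zero overlap follows from the stated limits alone. The 83% coverage assumes two words before the verb, as in Table 2. The detection rates are illustrative and rest on assumed variances. The documents give no evidence that a difference in the last 200 ms exists, and nothing here makes the permutation test invalid. This is a worthwhile, inexpensive improvement to a supporting check, and it makes the check address a risk that the article itself names.

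**What to change.** 1. Extend the check segment from -1400 to -200 ms to -1400 to 0 ms relative to verb onset. Baseline it on the pre-sentence interval (-1400 to -1200 ms) and do not apply the verb baseline to it.
2. Compare the voices over -1200 to 0 ms, and report the active-passive difference over -200 to 0 ms separately.
3. Prespecify that, if -200 to 0 ms differs, the verb cluster test is rerun with the pre-sentence baseline as a sensitivity analysis. The planned 200 ms baseline stays primary. The rerun needs one segment from -1400 to +1000 ms (1400 + 1000 = 2400 ms).
4. If any item has more or fewer than two words before the verb, set its pre-sentence limits from its own first-word onset.

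The cost is one changed epoch limit and one extra comparison. The EEG is recorded continuously, so no new data or session time are needed. The sensitivity analysis will be somewhat noisier than the primary one, because its baseline lies further from the verb, and the longer segment may lose a few more trials to artefacts.
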